## Abstract

**Background:**

Low back pain (LBP) is a common musculoskeletal condition and, globally, a leading cause of years lived with disability. It leads to reduced social participation, impaired quality of life, and direct and indirect costs due to work incapacity. A coordinated approach focusing on psychosocial risk factors, active reeducation, and the early use of tools to maintain employment, may be effective for improving prognosis of patients with LBP. Primary care professionals and multidisciplinary teams, who see patients in the early stages of LBP may be in the best position to implement such a coordinated approach. We designed this study to assess a coordinated multi-faceted strategy in primary care for patients with subacute or recurrent acute LBP.

**Methods:**

The CO.LOMB study was designed as a multicentric, cluster-randomized, controlled study. Patients aged 18–60 years, with subacute or recurrent acute LBP are eligible. Patients also need to be employed (but can be on sick leave) with access to occupational health services. The clusters of GPs will be randomized (1:1) to either the Coordinated-care group or the Usual-care group. Patients will be assigned the group allocated to their GP. The healthcare professionals (GPs and associated physiotherapists) allocated to the Coordinated-care group will perform a 2-session study training. The following interventions are planned in the Coordinated-care group: exploration and management of psychosocial factors, active reeducation with a physiotherapist, the implementing of tools to maintain employment, and a reinforced cooperation between primary healthcare professionals. The primary objective is to assess the benefit of coordinated primary care to reduce disability in LBP patients at 12 months after enrollment: measure using the validated French version of the Roland Morris Disability Questionnaire. Secondary objectives include the evaluation of pain, work status, and quality of life at various time points. The study plans to enroll 500 patients in 20 GP clusters. Patients will be followed up for 12months.

**Discussion:**

This study will evaluate the benefit of a coordinated multi-faceted strategy in primary care for patients with LBP. Notably whether this approach will alleviate the associated disability, attenuate pain, and promote the maintenance or return to work.

**Clinical Trial Registration:**

NCT04826757.

**Graphical Abstract fig1:**
[figure not shown]

## Background

Low back pain (LBP) is a common musculoskeletal condition. Worldwide, in 2019, 568.4 million suffered from LBP, with an estimated age-standardized point prevalence of 6972.5 per 100,000 people (7.0%) (1). In Western Europe, the estimated age-standardized point prevalence was 9445.4 per 100,000 people (9.4%) (1). Even more concerning, globally in 2017, LBP was the leading cause of years lived with disability (2).

LBP can be classified according to its duration: acute (pain lasting less than 4 weeks), subacute (pain lasting between 4 and 12 weeks), and chronic (when pain has been present for more than 12 weeks). For most people, LBP improves noticeably during the first 4–6 weeks (3). After this period, LBP improves at a slower rate. At 1 year, many patients still experience low to moderate levels of pain and disability (3). Chronic or recurrent LBP is characterized by functional disability but is also accompanied by psychosocial problems, including anxiety, depression, reduced social participation, eroded family relationships, impaired quality of life, and either temporary or extended work incapacity (4–6). There are direct healthcare costs associated with LBP treatment (4, 5, 7, 8), but also, substantial indirect costs, particularly those related to prolonged work incapacity.

The traditional biomechanical approach of prescribing rest and pain medication are often ineffective (9). The biopsychosocial model for LBP emphasizes the importance of psychosocial risk factors, including psychological, psychiatric, occupational, and social factors. These factors significantly impact LBP and increase the risk for chronic LBP (10). This LBP model suggests that optimal management may be a coordinated multi-faceted strategy targeting different types of risk factors and involving various healthcare professionals.

Most patients with LBP consult general practitioners (GPs) and physiotherapists. Indeed, a French study found that 77% of patients with LBP consulted GPs and 30% underwent physiotherapy (11). Furthermore, occupational healthcare professionals in coordination with GPs play a key role in maintaining employment in these patients (12). In France, all employed workers as well as some self-employed workers have access to an occupational physician (OP) or an occupational nurse, depending on the location of their company. Comprehensive and coordinated care are critical components of primary care, with GPs playing a central role.

In this study we aim to assess the benefit of a coordinated multi-faceted primary care strategy for reducing disability, compared to usual care, in patients, aged between 18 and 60 years, with subacute or recurrent acute LBP.

## Method/design

### Study design

The CO.LOMB study was designed as a multicentric, cluster-randomized, controlled study. The clusters corresponded to at least 4 GPs practicing in the same geographic area (most often within the same multidisciplinary team). The clusters of GPs identified are located in 4 geographic regions: each attached to a University Department of General Practice (Angers, Nantes, Rennes, and Nice). The clusters will be randomized to either coordinated primary healthcare (the Coordinated-care group) or usual care (the Usual-care group).

### Study population

All patients, presenting with LBP at the practices of GPs participating in the study, will be considered for study participation. The eligibility criteria for the study are as follows:

#### Inclusion criteria

Patients need to meet the following criteria to participate in the study:

Patients aged between 18 and 60 years old.Patients consulting a GP with LBP, defined as a pain situated between the 12th rib and the gluteal cleft. The LBP must be either:

Subacute LBP, defined as back pain lasting between 4 and 12 weeks and preceded by at least 30 days without back pain.Acute recurrent LBP, defined as back pain lasting for less than 4 weeks and preceded by at least 30 days without back pain. The patients must have consulted a healthcare provider for LBP within the previous 12 months.

3. Patients must be employed (but can be on temporary sick leave) at enrollment.4. Patients must have access to occupational health services (working for a company that either has its own OP or a company using shared occupational health services).5. Patients must provide signed consent to participate in the study.6. Patients must be registered with a social security scheme.

#### Non-inclusion criteria

Patients meeting any of the following criteria will not be eligible for the study:

Patients with a specific LBP, including LBP due to fractures, infections, osteoporosis, inflammatory diseases, or tumors (with confirmed diagnosis or highly suspected, resulting in specific and/or urgent treatment).Patients with LBP with pain irradiating below the knee.Patients for whom active reeducation is contraindicated.Patients performing follow-up for their LBP with a GP not participating in the study.Patients performing reeducation with a physiotherapist not participating in the study and who are unwilling to change physiotherapist (Interventional group only).Patients planning to leave the study territory within the 12 months following study enrollment.Patient planning to retire within the 12 months following study enrollment.Pregnant, breastfeeding, or parturient women.Patients undergoing psychiatric care under duress.Patients admitted into a social or healthcare center for a reason other than for research.Patients unable to read and write in French.Persons deprived of their liberty by judicial or administrative decision.Adult patients under legal protection measure (guardianship).Persons unable to provide consent.

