### Randomization

GPs will be cluster randomized for the study. The clusters of GPs will be randomized, in a 1:1 ratio, to either the Coordinated-care or the Usual-care group. The randomization will be stratified by the geographical region related to the University Department of General Practice (Angers, Nantes, Rennes, and Nice). The study plans to enroll 20 GP clusters distributed as follows: 10 clusters for the Department of General Medicine attached to Angers (5:5), 4 for each of those attached to Nantes (2:2) and Rennes (2:2), and 2 for that attached to Nice (1:1). The randomization of the clusters for the Department of General Medicine attached to Angers (10 clusters) will also be stratified by the time of study initiation, since the synchronous initiation of the clusters in Angers is not feasible. The randomization will be performed by the Biostatistical Department of the University Hospital Center (“CHU”) at Angers. All patients followed up in the same cluster will be allocated the same group as their GP.

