### Interventions

Prior to the study, all healthcare professionals (GPs and associated physiotherapists) in the clusters allocated to the Coordinated-care group will undergo a 2-session training for the study interventions. The training sessions will be performed within each of the 10 clusters. Each training will be comprised of two sessions separated by a 2-to-4-week time interval. The first 90-min training session will focus on three blocks: the factors that may influence the evolution and treatment of LBP, the French recommendations that promote active LBP management with therapeutic education (13), and the tools available for maintaining employment in patients with LBP. This first session will be performed autonomously by GPs and physiotherapists, guided by a video. The professionals will be asked to produce a written summary of their exchanges on each block. During the 2–4-week interval between the training sessions, the GPs and physiotherapists will be invited to complete auto-observation questionnaires concerning any patients with LBP that consult them. The second session will consist of a three-and-half-hour in-person training, at each cluster’s location, by the clinical training team: made up of the same doctor and physiotherapist. In addition, the clinical training team will systematically invite a local OP to this second session. The session will combine formal presentations related to each interventional component (psychosocial factors in LBP, active exercise reeducation program for patients with LBP, and the tools to maintain employment). The training session will also include several periods of time for the health care professionals to exchange their clinical experiences, and to propose ways to evolve their practices to incorporate the elements associated with the study intervention. During the session there will be a final sequence focusing on interprofessional collaboration, during which the healthcare professionals will decide on the modalities for collaboration to be implemented in the study.

The aim of the training will be for the healthcare professional to appropriate the concepts, tools, and interventions applied during the study. During the training, healthcare professionals will also discuss various aspects of healthcare including care providers, resources offered in the region, as well as potential barriers to collaboration, and how to overcome these barriers.

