This multi-faceted study intervention was designed as a coordinated and comprehensive biopsychosocial healthcare strategy. The intervention is fundamentally patient centered: adapted to the needs and preferences of each patient. The healthcare professionals must evaluate the pertinence of each part of intervention according to the patient’s specific situation, and to incorporate the patient’s preferences in the treatment decision, following a shared decision approach. The patient will remain free to accept or not, or to delay, any proposed part of intervention without being excluded from the study.

Patients in clusters allocated usual care are treated according to the GP’s usual practice.

To avoid creating a feeling of injustice in healthcare professionals allocated the non-intervention group and to motivate them to actively participate in the study, the 2-session training will be offered to physicians and physiotherapists of these clusters after the end of the study.

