### Sample size

To calculate the sample size required for the study we hypothesize that 50% of patients in the control group (Usual-care group) and 70% of those in the interventional group (Coordinated-care group) will have a significantly reduced disability at 12 months after being enrolled (3, 33). Considering a cluster randomized study with the following statistical characteristics:

A power of 80%.A type 1 error (α-risk) of 0.05.A mean cluster size of 25 patients.A coefficient of variation in the cluster size of 0.2.An intraclass correlation coefficient of 0.03.An attrition rate of 20%.

To show a difference of 20% between the study groups (70% vs. 50%) the study needs to include 10 clusters of 25 patients in each study group. Therefore, a total of 20 clusters of 25 patients: 500 patients are required for the study. The sample size was calculated using Stata (Stata 13.1 software, package clustersamplsi).

This sample size is realistic considering that GPs on average perform 2,500 consultations per year in patients aged between 18 and 60 years (34). Among these 1 of every 200 consultations concerns subacute LBP (35). Therefore, on average 12–13 patients per year with subacute LBP consult each GP in France. The number of consultations for recurrent acute LBP is more difficult to estimate but is about as frequent as those for subacute LBP. The planned patient enrollment period is 24 months for any given cluster. Each cluster will consist of at least 4 GPs. Therefore, the study target of recruiting 25 patients per cluster is feasible. The total planned enrollment period is 36 months, comprising an initial 12-month period during which the clusters will be initiated followed by a 24-month patient enrollment period.

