### Statistics

Quantitative data will be presented as means with standard deviations and will be compared using Mann–Whitney tests. Qualitative data will be presented as numbers with percentages and compared using Fisher’s exact tests.

For the primary objective, the proportion of patients that have an improved (lower score) of at least 4 points, in the RMDQ, at 12 months after enrollment will be compared in the study groups. The analysis will be performed using a multilevel logistic mixed model that will allow the clustering effect to be considered as random.

Similarly, the secondary outcome measures with binary outcomes compared between the study groups (e.g., the proportion of patients that improved by at least 2 points on the numerical pain scale at 12 months) will be analyzed by multilevel logistic mixed regression models.

Secondary outcome measures assessing changes in a quantitative parameter over time (e.g., the evolution of the RMDQ scores measured at baseline and then at 3, 6, and 12 months after enrollment) will be analyzed using linear multilevel mixed regression models. The individual effect will be included in the cluster effect. Time will be considered as qualitative variables with a varying number of modalities, e.g., 4 modalities for outcomes assessed at baseline, and then at 3, 6, and 12 months, and 3 modalities for outcomes assessed at baseline, and then at 3 and 6 months. The effect of the intervention will be evaluated by including an interaction between the variables for time and for the study group. The effect of the intervention will be assessed at each time point. The increased alpha-risk, due to multiple analyses, will be accounted for using the Bonferroni correction.

For these various multilevel models, the variance–covariance matrices will be considered as unstructured. Missing data will be treated using a set of 10 multiple imputations based on chained equations (38, 39). The analyses will be performed bilaterally with the alpha-risk set at 5%, except in cases where the Bonferroni correction was used. The data will be analyzed on an intent-to-treat basis. Thus, all patients with data will be included in the analysis unless they specifically indicate that they do not want their data analyzed.

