GPs in the interventional group may preferentially include patients with severe LBP instead of enrolling all eligible patients if they consider the intervention to be better than usual care, and that this improved care may benefit patients with severe LBP more than patients with less severe LBP. This phenomenon may also occur in the control group, where GPs may be reluctant to suggest study participation because of the protocol’s constraints, to patients with non-severe LBP. We have examined this issue and will address this by providing continuous support for GPs during the study. Where a significant difference between groups in terms of patient’s LBP status at baseline is observed, we planned to adjust analyses to limit the impact of this bias on the results.

Most studies that have assessed the clinical evolution of LBP have used either pain, incapacity, and/or returning to work to measure the effectiveness of interventions (33, 49). However, from a patient’s perspective, reduced LBP is mainly comprised of three dimensions: attenuated pain, improved functional capacity, and combined with an acceptable quality of life, which includes the capacity to work (24). In our study, we chose perceived disability, considered by patients to be of utmost importance, as our primary outcome measure. However, we have included several secondary outcome measures, including measures to assess pain, quality of life, and the patients’ occupational status—other important facets of LBP.

Currently, in France, primary healthcare professionals, working in the same geographical region, are encouraged to group together in multidisciplinary practices. Our study is consistent with this evolution of primary healthcare, evaluating a coordinated strategy composed of a multidisciplinary team. Moreover, our study allows healthcare professionals in each region to form networks that hopefully will persist after the study has been completed. Consequently, we will cluster randomized GPs in the same region to promote local cooperation among professionals.

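### One non-inclusion criterion applies in the Coordinated-care arm only, so the two arms enroll different populations by rule; the size and direction of the resulting bias are unknown and the size may be small

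*Protocol article*

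**What the plan says.** The Non-inclusion criteria section of the protocol article opens with "Patients meeting any of the following criteria will not be eligible for the study". One item in the list reads "Patients performing reeducation with a physiotherapist not participating in the study and who are unwilling to change physiotherapist (Interventional group only". It is the only item in the list limited to one arm. The neighbouring item on follow-up by a non-participating GP applies to both.

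On allocation, the Randomization section says "All patients followed up in the same cluster will be allocated the same group as their GP". The Interventions section says "Prior to the study, all healthcare professionals (GPs and associated physiotherapists) in the clusters allocated to the Coordinated-care group will undergo a 2-session training". The Discussion adds that each group has its own patient information and consent letter.

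On refusal of components, the Interventions section says "The patient will remain free to accept or not, or to delay, any proposed part of intervention without being excluded from the study". The same section describes the physiotherapy programme as something patients will have access to, not as a condition of taking part.

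On analysis, the Statistics section says "The data will be analyzed on an intent-to-treat basis". For selective inclusion, the Discussion considers LBP severity and says "Where a significant difference between groups in terms of patient’s LBP status at baseline is observed, we planned to adjust analyses". It does not mention the physiotherapist criterion.

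**The concern.** Eligibility is judged when the arm is already known, by a rule that differs between arms. Patients who are already treated by an outside physiotherapist and will not move are removed from one arm and kept in the other. Such patients may differ from the rest in current care, treatment preference and expectations. The Discussion itself says that expectations are associated with prognosis and relies on the randomized design to limit confounding from them. Here the design cannot do so, because the filter acts on patients after the clusters are randomized. The primary outcome is a self-completed questionnaire in an unblinded trial, so differences in preference and expectation may well show in it. At stake is a systematic difference in the 12-month responder proportion that is not an effect of the intervention.

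**Working it through.** **Step 1. Order of events.** Clusters are randomized, professionals in intervention clusters are trained before the study, and patients take the arm of their GP. Consent letters are arm-specific, and the criterion itself can be applied only by someone who knows the arm. The filter is therefore post-allocation and one-sided.

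**Step 2. The plan's own figure.** Inputs from the Sample size section: 50% vs 70% responders, power 80%, alpha 0.05 (two-sided per the Statistics section), mean cluster size 25, coefficient of variation 0.2, ICC 0.03, attrition 20%.
- Design effect = 1 + ((0.2² + 1) × 25 − 1) × 0.03 = 1 + 25 × 0.03 = 1.75.
- Cluster-level t-test with 2(k − 1) degrees of freedom: 7 clusters per arm give power 0.772 and 8 give 0.834, so 8 are needed.
- Attrition: 8 / 0.80 = 10 clusters per arm, and 20 × 25 = 500. The stated total is reproduced and is not in question here.

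**Step 3. Size of the bias.** Let f be the share of otherwise eligible patients removed by the rule, and d the gap in 12-month responder probability between those kept (p_k) and those removed (p_r). With no true effect, the control arm responds at f × p_r + (1 − f) × p_k and the intervention arm at p_k. The difference is f × (p_k − p_r) = f × d. The documents give neither f nor d, so both are assumptions:

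| f | d = 10 points | d = 20 points | d = 30 points |
|---|---|---|---|
| 2% | 0.2 | 0.4 | 0.6 |
| 5% | 0.5 | 1.0 | 1.5 |
| 10% | 1.0 | 2.0 | 3.0 |
| 20% | 2.0 | 4.0 | 6.0 |

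Entries are percentage points of bias. The sign favours the intervention if the removed patients have a worse prognosis, and goes against it if they have a better one.

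**Step 4. Effect on type I error.** After 20% attrition there are 20 analysed patients per cluster, hence 10 × 20 = 200 per arm.
- Design effect = 1 + (1.04 × 20 − 1) × 0.03 = 1.594.
- Effective size per arm = 200 / 1.594 = 125.5.
- Standard error with 50% responders in both arms = √(2 × 0.25 / 125.5) = 0.063, that is 6.3 points.

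With a normal approximation, the two-sided type I error is:

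| Bias (points) | Type I error |
|---|---|
| 1 | 5.3% |
| 2 | 6.2% |
| 3 | 7.6% |
| 6 | 15.8% |

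**Step 5. Where f is likely to lie.** The Background reports that 30% of patients with LBP underwent physiotherapy. The criterion needs more than that: reeducation in progress at enrollment, with a non-participating physiotherapist, and unwillingness to change. Eligible patients have had pain for at most 12 weeks, after at least 30 pain-free days, which leaves little time for this. A share of 20% would require 0.20 / 0.30, or two thirds, of all physiotherapy users to meet every condition. The upper rows of the table in Step 3 are the more plausible ones.

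**The case against.** The strongest reply is that the rule is harmless in practice and serves a purpose. It keeps in the intervention arm people who can actually receive the trained physiotherapist's programme. Few patients will meet all its conditions, so the bias may be under one point against a 20-point target. All of this may be true, and it limits the size of the finding. It does not remove the asymmetry, and the article does not describe a way to measure it.

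A reader might infer three stronger things that the documents do not support.
- **That intent-to-treat is violated.** It is not. That principle governs how enrolled patients are analysed, and the criterion acts before enrollment.
- **That the Interventions section flatly contradicts the criterion.** Read literally, it protects a patient already in the study who declines or delays a component, whereas the criterion screens at entry. The tension is one of principle: refusing the trained physiotherapist after enrollment is allowed, while refusing to leave an outside one beforehand bars entry.
- **That a 6-point bias should be expected.** That figure multiplies the two most extreme assumptions.

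It also stands that removing the rule has a price: the patients whose exclusion causes the bias are the ones who would dilute the effect if enrolled. And a symmetric version of the rule is hard to define, because control patients have no trained study physiotherapist to change to, so a question about willingness would be hypothetical for them.

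**Conclusion.** The point holds as a design asymmetry that is certain in the current text. The enrolled populations differ by rule, and neither cluster randomization nor the conditional adjustment for LBP status corrects this, because current outside physiotherapy and willingness to change are not LBP status. The consequence is uncertain. The illustrative range is 0.2 to 6 points, resting on an assumed excluded share of 2 to 20% and an assumed responder gap of 10 to 30 points. The low end is more likely, and the direction is unknown. At 1 to 2 points the type I error would be about 5.3 to 6.2%, against a nominal 5%. The sample size of 500 is unaffected. The case for acting is that the change is small and that analysis can repair the problem only in part once recruitment is over.

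**What to change.** **Further enrollment.** Delete the arm-specific criterion by amendment. Enroll these patients in both arms, analyze them in the arm of their cluster, and record which physiotherapist they use as a measure of adherence. This fits the freedom to decline components that the Interventions section already grants. At the date in the Trial status section, 41 of 500 patients were enrolled, so a change then would have covered 459 / 500 = 91.8% of the planned sample.

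**Cost.** One line in the eligibility list, plus a dilution proportional to the share of such patients. If they gained nothing at all from the rest of the intervention, the loss would be at most f × 20 points: 0.4 points at f = 2% and 4 points at f = 20%.

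**Patients already enrolled.** Report the number refused under this rule in the intervention clusters. Where physiotherapy at baseline was recorded in both arms, add a prespecified analysis adjusted for it. This is only a partial repair, because willingness to change may not be known for control patients. Do not simply drop every control patient with an outside physiotherapist. That would also remove those who would have been willing to change, whose counterparts remain in the intervention arm, and so create the reverse imbalance.
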